#### 4.2 Method for randomisation

Central randomisation will be performed by an online, secure, software application (Sealed Envelope; <https://www.sealedenvelope.com>). The group of intervention will be automatically assigned following a pre-established randomisation list completed by the statistician of the study. The allocation ratio between the HDT15 (intervention) and usual position (control) groups will be 1:1. Randomisation will be stratified by site. To take into account the inter-individual heterogeneity in baseline collateral status, randomisation will also be stratified according to score of the National Institute of Health stroke scale (NIHSS) at presentation in the Emergency Room (dichotomised 0 to 5 versus 6 or more), which will be assessed before treatment allocation. Patients with NIHSS 0 to 5 will be considered as having a “minor stroke” despite a M1 occlusion, which will be considered as a surrogate marker of good baseline collaterals.

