#### 4.3.2 Secondary endpoints

Secondary endpoints will further assess:

i. **feasibility** outcomes:

- proportion of patients randomised to the intervention group who are able to maintain HDT15 during the entire MT procedure, encompassing patient tolerance, the ability to perform MT at -10° to -15° tilt and any other reasons for premature treatment termination;
- hospital admission-to-arterial access time (i.e. time to arterial puncture);

ii. **safety** outcomes:

- Mean values of systolic blood pressure, diastolic blood pressure and oxygen saturation from hospital admission to the end of MT; these physiological parameters will be monitored at entry in the Emergency Room, at entry in the angio suite and every 15 minutes from the start to the end of MT
- Proportion of patients presenting one or more episodes of vomiting from randomisation to the completion of MT
- Proportion of patients who had increase of  $\geq 4$  points on the NIHSS score within 24 $\pm$ 12 hours of the randomisation;
- Proportion of patients who had SICH per SITS-MOST definition within 24 $\pm$ 12 hours: type 2 parenchymal hematoma with neurological deterioration of  $\geq 4$  points on the NIHSS;
- proportion of patients with pneumonia within the first 72 hours after randomisation;
- Safety data, including serious and non-serious adverse events, as well as reasons for HDT15 discontinuation (e.g. discomfort, vomiting, neurological worsening, headache, respiratory distress) and technical challenges related to MT will be reported for both treatment arms;

iii. **efficacy** outcomes:

- functional outcome at 3 months, assessed with the ordinal score on the modified Rankin scale (shift across outcomes on the mRS between groups);
- early neurological improvement before MT, at 24±12 hours and at 7 days or discharge (whichever comes first), defined as percent change in NIHSS score  $[(\text{Admission NIHSS} - \text{time-point NIHSS}) \times 100 / \text{Admission NIHSS}]$ .

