## **5 ELIGIBILITY CRITERIA**

### **5.1 Inclusion criteria**

- Adults ( $\geq 18$  years old)
- Acute ischemic stroke due to left or right proximal MCA occlusion (M1 segment; excluding concomitant occlusion of the ipsilateral internal carotid artery and/or not visible A1 segment of the ipsilateral anterior cerebral artery)
- Decision to treat with mechanical thrombectomy (with or without intravenous thrombolysis)
- Informed consent obtained from patient or patient's legal representative, or emergency consent procedure

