### **9.3 Statistical methods**

#### **9.3.1 General considerations**

The quantitative variables will be described by the following parameters: number of patients, number of missing values, mean, standard deviation (SD), median, first and third quartiles (Q1 and Q3), minimum and maximum. Categories could be defined if applicable using a cut-off threshold from literature or quantiles.

The qualitative variables will be described by the following parameters: number of patients, number of missing values, frequency and percentage of each modality (missing values will not be included in the denominator used for frequency computation).

The analyses will be performed using the R and SAS software. They will be performed by the biostatistics unit of the University of Milano-Bicocca.

After the end of the statistical analysis of the DOWN-SUITE study, a meta-analysis could be carried out with the French partner ([name], Hospices Civils de Lyon), who applied for funding for a similar study (DOWN-SUITE-Fr, the result of which is pending).

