#### ii. safety outcomes:

- Mean values of systolic blood pressure, diastolic blood pressure and oxygen saturation at entry in the Emergency Room, at entry in the angio suite and every 15 minutes from the start to the end of MT; they will be treated as continuous variables and calculated as mean with their 95% confidence interval for each group.
- Proportion of patients presenting one or more episodes of vomiting from randomisation to the completion of MT will be calculated with their 95% confidence interval for each group.
- Reasons for HDT15 discontinuation (e.g., intolerable discomfort, observed severe discomfort in non-communicative patients, vomiting, neurological worsening,

headache, or respiratory distress), minor adverse events, and MT-related technical challenges will be recorded and reported as proportions with 95% confidence intervals.

- The proportions of patients who had an increase of  $\geq 4$  points on the NIHSS score within  $24 \pm 12$  hours of the randomisation will be calculated with their 95% confidence interval for each group.
- The proportions of patients who had SICH within  $24 \pm 12$  hours will be calculated with their 95% confidence interval for each group.
- The proportions of patients with pneumonia within the first 72 hours after randomisation will be calculated with their 95% confidence interval for each group.
- Safety data, including serious and non-serious adverse events, as well as reasons for HDT15 discontinuation (e.g. discomfort, vomiting, neurological worsening, headache, respiratory distress) and technical challenges related to MT will be reported for both treatment arms. Adverse events will be categorized according to the Medical Dictionary for Regulatory Activities (MedDRA) v28.0.

iii. **efficacy** outcomes:

- functional outcome at 3 months, assessed with the ordinal score on the modified Rankin scale (shift across outcomes on the mRS between groups).
- Percent change in NIHSS ( $[(\text{Admission NIHSS} - \text{time-point NIHSS}) \times 100 / \text{Admission NIHSS}]$ ) from admission to immediately pre-MT, at  $24 \pm 12$  hours, and at  $7 \pm 2$  days (or discharge), calculated with 95% confidence intervals.

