#### **9.5 Method of taking missing data into account**

Analyses will be performed on data available. There will be no imputation of missing data.

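### Early neurological improvement divides by an admission NIHSS that may be 0 or very low, and death before a follow-up NIHSS removes a patient from this endpoint and from the 4-point deterioration rate

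*Protocol*

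**What the plan says.** **The efficacy measure.** Section 4.3.2 assesses early neurological improvement before thrombectomy, at 24±12 hours and at day 7 or discharge: "whichever comes first), defined as percent change in NIHSS score". Writing A for the admission score and T for the score at the time point, the measure is 100 × (A − T)/A. Section 9.3.3 repeats the formula, to be "calculated with 95% confidence intervals". No comparative model is attached to it. Section 9.3.1 lists mean, SD, median and quartiles for every quantitative variable.

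**Who can enter.** The inclusion list in 5.1 has no NIHSS threshold; its treatment criterion is "Decision to treat with mechanical thrombectomy (with or without intravenous thrombolysis"). The only NIHSS-based exclusion in 5.2 concerns item 1a. Section 4.2 plans for low scores and makes them a randomisation stratum: "Patients with NIHSS 0 to 5 will be considered as having a" minor stroke.

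**The deterioration rate.** Section 4.3.2 lists, as a safety outcome, "Proportion of patients who had increase of" at least 4 NIHSS points within 24±12 hours of randomisation. Section 9.3.3 reports it per arm with a 95% confidence interval. Neither place mentions death.

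**Missing data.** Section 9.5: "Analyses will be performed on data available. There will be no imputation of missing data". Section 9.3.1, on categorical variables: "missing values will not be included in the denominator used for frequency computation".

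**The concern.** The denominator of the efficacy measure can be 0 or close to it in patients whom the protocol expressly expects. At 0 there is no value and no rule for what to do. At 1 to 3 the scale is lopsided: improvement cannot exceed +100%, while worsening has no comparable limit. A mean with a confidence interval on such a scale may describe a few minor-stroke patients rather than the arm.

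The second part concerns deaths. A patient who dies before the follow-up score has no NIHSS at that time point. Under the available-data and denominator rules, that patient leaves both the improvement summary and the deterioration rate. Neurological deterioration is a named safety objective (3.2), so the rate would omit some of the worst early courses.

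**Working it through.** **1. The percent-change scale**

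Inputs: the formula from 4.3.2 and 9.3.3; eligibility from 4.2, 5.1 and 5.2; 59 patients per arm from 9.1. The protocol gives no planning figure for the NIHSS endpoint. The arm size itself reproduces by the unpooled normal approximation: (1.960 + 0.842)² × (0.60 × 0.40 + 0.35 × 0.65)/0.25² = 58.7, hence 59. It serves here only as the arm size.

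Because T cannot be below 0, 100 × (A − T)/A cannot exceed +100%. For worsening:

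| Admission NIHSS | 4-point worsening | 10-point worsening |
|---|---|---|
| 0 | undefined | undefined |
| 1 | -400% | -1000% |
| 2 | -200% | -500% |
| 3 | -133% | -333% |
| 5 | -80% | -200% |
| 6 | -67% | -167% |
| 15 | -27% | -67% |
| 20 | -20% | -50% |

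Leverage of one patient on the mean of a 59-patient arm (assumed cases):

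- NIHSS 2 to 6, the other 58 at +40%: (58 × 40 − 200)/59 = 35.9%, instead of 40.0%.
- NIHSS 2 to 12, the other 58 at +40%: (58 × 40 − 500)/59 = 30.8%.
- NIHSS 1 to 15, a deliberately extreme case: (1 − 15) × 100/1 = -1400%, which contributes -1400/59 = -23.7 percentage points to the arm mean.

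In the first two cases the median stays at 40%. A median does not, however, give a value to a patient admitted with a score of 0.

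**2. Deaths before a follow-up score**

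The deterioration endpoint needs a recorded rise. Section 9.5 allows no imputation, and 9.3.1 takes missing values out of the denominator. No section gives a patient who dies a score or an event status. Together these remove a patient who dies before any follow-up NIHSS is recorded.

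The documents give no early death rate, so the counts below are assumptions.

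- One arm of 59, with 5 recorded rises and 3 deaths before a follow-up score. Available data: 5/(59 − 3) = 5/56 = 8.9%. Deaths counted as events: (5 + 3)/59 = 13.6%.
- Two arms of 59, with 6 recorded rises in each, and 1 against 5 such deaths. Available data: 6/58 = 10.3% against 6/54 = 11.1%. Deaths counted as events: 7/59 = 11.9% against 11/59 = 18.6%. The difference shrinks from 6.8 points (4/59) to 0.8 points.

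**The case against.** **On percent change.** Section 9.3.3 does not name the mean, 9.3.1 also reports medians, and no between-arm test is specified for this endpoint. A reader might infer that the trial would reach a wrong comparative conclusion. The documents do not support that: what is at risk is a descriptive mean and its interval. Nor is it an error in itself that equal absolute changes give different percentages; any relative measure does that. A score of exactly 0 must also coincide with a decision to perform thrombectomy, which may be rare. What stands is the missing value at 0 and the instability just above it, in a stratum the protocol created itself.

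**On deaths.** The protocol nowhere says that a death is a missing value, and a rule for death is often left to the analysis plan. But 9.3.1 and 9.5 are positive statements, and a worst-rank score for death would depart from 9.5 as written. A rise of at least 4 points recorded before death can still count, so not every early death is lost.

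A reader might also infer that a lethal effect would show up as less deterioration. That goes too far. In the two-arm illustration the difference shrinks but does not reverse. Deaths are also reported as serious adverse events for both arms, enter the 3-month mRS, and fall within the monitoring board's periodic safety review (8.4).

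**On SICH.** A reader might extend the argument to fatal haemorrhage, because 4.3.2 requires a 4-point NIHSS deterioration alongside a type 2 parenchymal hematoma. The protocol ties this to a cited definition that is not at hand, so it cannot be said that fatal cases are lost. It can only be said that their handling without a recorded NIHSS should be stated.

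**Conclusion.** The point holds for secondary endpoints. The improvement measure is undefined at an admission score of 0 and unstable at 1 to 3, both of which the protocol admits; its mean and 95% confidence interval can be dominated by a few minor-stroke patients. Under the available-data rules, patients who die before any follow-up NIHSS also leave this measure and the 4-point deterioration rate. This second part follows from 9.3.1 and 9.5 taken together and is not an explicit statement.

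The scale values are exact arithmetic. The effect on arm means and on the deterioration rate is illustrative, because the documents give neither the share of patients with low NIHSS nor early mortality. The primary endpoint and the sample size are unaffected. The change is worth making because it is cheap, not because it threatens the trial's main conclusion.

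**What to change.** - **4.3.2 and 9.3.3, improvement:** replace percent change by NIHSS at each time point (or absolute change), adjusted for admission NIHSS as a continuous variable, preferably on a rank or ordinal scale with death ranked worst. If wanted, keep percent change as a descriptive summary for patients with admission NIHSS above 0.
- **4.3.2 and 9.5, deterioration:** state that death before the 24±12 hour assessment counts as an event in this analysis, or report deterioration-or-death beside the existing rate.
- **4.3.2, SICH:** state how a fatal type 2 parenchymal hematoma without a recorded NIHSS is counted, consistent with the cited definition.

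**Cost.** No new data are needed, since admission NIHSS and deaths are already collected. A secondary endpoint is redefined, which takes a protocol amendment; the version record in 1.2 lists an undated fourth amendment that could carry it. Section 9.4 plans an interim analysis of secondary outcomes 12 months after recruitment starts, so the change should be made and documented without reference to unblinded interim results.

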## **5 ELIGIBILITY CRITERIA**

### **5.1 Inclusion criteria**

- Adults ( $\geq 18$  years old)
- Acute ischemic stroke due to left or right proximal MCA occlusion (M1 segment; excluding concomitant occlusion of the ipsilateral internal carotid artery and/or not visible A1 segment of the ipsilateral anterior cerebral artery)
- Decision to treat with mechanical thrombectomy (with or without intravenous thrombolysis)
- Informed consent obtained from patient or patient's legal representative, or emergency consent procedure

### **5.2 Exclusion criteria**

- Impaired consciousness, defined as NIHSS score of 2 or 3 of the item 1a (level of consciousness): not alert, requires repeated stimulation or unresponsive.
- Vomiting upon stroke onset.
- History of glaucoma.
- History or imaging findings of intracranial hypertension of any aetiology
- Major breath disorders, defined as follows:
  - oxygen saturation  $\leq 92\%$  in room air at admission
  - severe chronic obstructive pulmonary disease (COPD) treated with long-term oxygen therapy.
  - severe heart failure with NYHA class 3 or 4 (breathlessness during ordinary physical activity or at rest).
- Severe obesity, defined as body mass index (BMI)  $> 35$ .
- Patients participating in another interventional trial that would interfere with this study.
- Female patients who are pregnant

### **5.3 Premature study exit criteria**

The criterion for premature study exit for a patient is the withdrawal of consent.

Early withdrawal will not affect standard of medical care. Patients with premature exit from the study will not be replaced.

### **5.4 Criteria for discontinuation of study procedure**

HDT15 will be discontinued in cases of patient-reported intolerable discomfort, observed severe discomfort in non-communicative patients, or at the treating physician's discretion for clinical reasons (e.g., vomiting). All reasons for discontinuation will be recorded and reported as safety data.

### **5.5 Recruitment procedures**

Patients will be included at admission in the stroke emergency room of academic hospitals, each including a comprehensive high-volume stroke center. The DOWN-SUITE will start in three Italian centers, but an extension to other clinical sites may be considered, depending on available funding and the progress of the study.

After the baseline neuroimaging, including intracranial vascular imaging, the study investigator will check all inclusion and exclusion criteria and assess the patient's eligibility for the study. After the consent process and randomisation, the intervention will be performed as soon as possible in all patients.

## **6 EXPERIMENTAL STRATEGIES**

### **6.1 Study strategy: experimental group**

#### **6.1.1 Description of the strategy**

HDT15 will be applied in the intervention group in 2 different settings:

- in the Emergency Room, by tilting the stretcher to lower the head by -10° to -15° relative to the body of the patient; the degree of tilting will be checked using a dedicated digital inclinometer or a mobile phone app
- in the Angiography Suite, by tilting the angiography table to lower the head by -10° to -15° relative to the body of the patient, depending on the actual technology of the angiography system of each clinical site; the degree of tilting will be automatically checked using the angiography system

HDT15 will start as soon as possible following randomisation in the Emergency Room (i.e. after vascular neuroimaging), and will be maintained during the transfer to the Angiography Suite, as well as during the entire thrombectomy procedure: i.e. HDT15 will end after the completion of MT, when the patient is transferred from the angiography table to her/his bed in a standard flat position.

Application of HDT15 will not delay usual care. The standard in-hospital patient pathway, including transfer from neuroimaging room to the angiography suite and the required procedural steps of MT, will allow sufficient time for the application of HDT15. HDT15 duration is expected to be at least 30 minutes (estimated time 30 to 90 minutes), from start to the assessment of the primary efficacy endpoint.

The actual degree of HDT15 will be between -10° to -15°, depending on the ER stretchers and the angiographic system of each clinical site.

Despite conscious sedation being the preferred approach for MT in participating centers, for patients needing intubation, the HOB will be briefly set to 0° during tube placement to ensure safety, with immediate repositioning to the assigned position (HDT15: -10° to -15°; control: 0° to +30°) post-intubation to maintain protocol adherence.

#### **6.1.2 Justification of the chosen strategy**

No collateral therapeutic has been currently validated (see paragraph 2.1). There is no consensus in current clinical practice regarding the most appropriate head position for AIS patients. Both experimental and available clinical data on HDT15 suggest its potential benefit in boosting the collateral circulation with a very favorable safety profile. Moreover, the simplicity and low cost of HDT15 will have profound implications on global AIS management if this strategy is validated.

#### **6.1.3 Description of contraindications**

There are no contraindications apart from those listed in the exclusion criteria list (See paragraph 5.2).

## **6.2 Strategy of comparison : control group**

### **6.2.1 Description of the strategy**

Patients randomised in the control group will be maintained in the usual position during the emergency room phase (0° to +30°) and on the angiography table (0°), according to standard practice. MT will be performed as per usual care.

### **6.2.2 Justification of the chosen strategy**

Patients in the control group will be managed according to standard practice.

### **6.2.3 Description of contraindications**

There are no contraindications apart from those listed in the exclusion criteria list (See paragraph 5.2).

## **6.3 Blinding**

### **6.3.1 Organisation**

Double-blinding of the study intervention is not possible. The Neurologist and Neurointerventionist in charge of the patient will remain in close proximity of the patient during HDT15 application, and cannot be blinded. Similarly, the patient cannot be blinded to the treatment allocation, given the nature of the procedure (HDT15 or flat position). Thus, this study is an open-label trial but with a blinded assessment of all endpoints, including the primary outcome, which will be assessed by a central imaging core lab.

### **6.3.2 Unblinding**

No unblinding procedure is planned for this study.

## **6.4 Permitted and prohibited associated treatments**

All treatments part of the standard management of AIS and/or deemed necessary by the treating medical team will be allowed during the study. The only prohibited treatment during the study will be experimental drugs or devices evaluated in other ongoing clinical trials.

## **7 GENERAL ORGANISATION**

### **7.1 Schedule of the study**

Duration of the inclusion period: 15 months

Duration of participation for each patient/healthy subject: 3 months  $\pm$  15 days

Total study duration: 18 months  $\pm$  15 days

Start of inclusions: Third quarter of 2024

The start of the study is defined by the first visit of the first patient (usually corresponds to the signing of the consent form). The end of the study is defined as the last visit of the last patient.

As soon as the first patient is included, the Sponsor must inform the competent Ethics Committee without delay of the effective starting date of the study (effective starting date = date of signature of the consent/date of receipt of the non-objection of the first person who takes part in the research).

## 7.2 Summary table

| Time point
Actions                                                     | Visit 1
Inclusion  | Visit 2                          | Visit 3                                      | Visit 4
Clinical visit
or Phone Call |
|-----------------------------------------------------------------------------------|--------------------------------------|-----------------------------------------|-----------------------------------------------------|------------------------------------------------------------|
|                                                                                   | Hospital
admission | Day 1
24±12
hours | Day 7±2
or hospital
discharge | Day 90±15
long-term
follow-up        |
| Eligibility screening                                                             | X                                    |                                         |                                                     |                                                            |
| Informed consent or emergency process                                             | X                                    |                                         |                                                     |                                                            |
| Brain neuroimaging                                                    | X                                    | X                                       |                                                     |                                                            |
| Randomisation                                                                     | X                                    |                                         |                                                     |                                                            |
| Study intervention (HDT15 or control)                                             | X                                    |                                         |                                                     |                                                            |
| Angiography / thrombectomy: ASITN/SIR collateral scale, TICI recanalisation score | X                                    |                                         |                                                     |                                                            |
| Demographic data                                                                  | X                                    |                                         |                                                     |                                                            |
| Medical history                                                                   | X                                    |                                         |                                                     |                                                            |
| mRS score                                                                         | X
pre-stroke               |                                         |                                                     | X                                              |
| Weight and height                                                                 | X                                    |                                         |                                                     |                                                            |
| ECG                                                                               | X                                    |                                         |                                                     |                                                            |
| Routine biological analysis                                           | X                                    | X                                       |                                                     |                                                            |
| Physiological parameters                                              | X                                    | X                                       |                                                     |                                                            |
| NIHSS score                                                           | X                                    | X                                       | X                                                   |                                                            |
| TOAST classification                                                  |                                      |                                         |                                                     | X                                                          |
| AE and SAE records                                                    | X                                    | X                                       | X                                                   | X                                                          |
| Any reasons for HDT15 discontinuation                                             | X                                    |                                         |                                                     |                                                            |

 Including intracranial vascular imaging, may be performed using either CT or MRI

 Routine biological analyses: complete blood count, glycaemia, sodium, potassium hepatic profile, serum creatinine and lipid profile (at 24h only), C-reactive protein.

 Physiological parameters: blood pressure, heart rate, oxygen saturation at inclusion (at entry in the Emergency Room; at entry in the angio suite; every 15 minutes from the start to the end of MT) and at 24 hours

 NIHSS score at admission will be measured both before enrollment and immediately before MT.

 mRS, AE/SAE and TOAST classification at 90 days may be collected via phone by a trained coordinator if in-person visit is not feasible.

